## Abstract

**Background:**

Previous experimental studies have found that ischemic post-conditioning exhibits neuroprotective effects by alleviating ischemia-reperfusion injury in an acute ischemic stroke model, and its efficacy is thought to be related to the duration of ischemic post-conditioning. However, ischemic post-conditioning has not been used in patients with acute ischemic stroke. This study aims to determine the safety, tolerability, and maximum tolerable duration of ischemic post-conditioning in patients with acute ischemic stroke receiving mechanical thrombectomy.

**Methods:**

Patients with acute ischemic stroke with unilateral middle cerebral artery M1 segment occlusion eligible for mechanical thrombectomy will be enrolled. We adopt a 3 + 3 dose-escalation design with a duration escalation schedule of 0, 1, 2, 3, 4, and 5 min × 4 cycles for the ischemic post-conditioning study. After successful reperfusion following mechanical thrombectomy, the balloon for ischemic post-conditioning will be inflated at the site proximal to the culprit lesion four times for 0–5 min with low-pressure (3–4 atmospheres) inflations, each separated by 0–5 min of reflow. We pre-defined the major responses (vessel perforation or rupture, reocclusion of the culprit vessel after ischemic post-conditioning, vessel dissection, severe vasospasm, ischemic post-conditioning related thrombotic events, and rupture of the balloon used for ischemic post-conditioning) as the stopping rules. Each patient will undergo a rigorous evaluation to determine the safety, tolerability, and maximum tolerable duration of ischemic post-conditioning.

**Discussion:**

This will be the first clinical study to ascertain the safety and tolerability of ischemic post-conditioning in patients with acute ischemic stroke receiving mechanical thrombectomy. The maximum tolerable duration obtained in this study will also serve as a starting point for future studies on the efficacy of ischemic post-conditioning.

**Clinical trial registration:**

[https://clinicaltrials.gov], identifier [NCT05153655].

## Introduction

Acute ischemic stroke, the most common type of stroke, is caused by decreased cerebral blood flow due to occlusion of cerebral arteries (Campbell and Khatri, 2020). Recanalizing the occluded vessels and restoring the reperfusion of the tissue at risk are the key strategies for the treatment of acute ischemic stroke. Mechanical thrombectomy is a standard recanalization therapy and has been recommended by guidelines after multiple randomized clinical trials have demonstrated that mechanical thrombectomy improved patient outcomes compared to standard medical therapy alone (Powers et al., 2018). However, even after mechanical thrombectomy, less than 50% of patients are functionally independent at 90 days, and mortality exceeds 15% (Goyal et al., 2016). Previous studies have focused on the role of inflammation in the pathogenesis of ischemic stroke and its relationship with reperfusion mechanisms (Pinto et al., 2006; Tuttolomondo et al., 2015, 2016). Recently, ischemia-reperfusion injury after recanalization is thought to play a prominent role in the poor prognosis of patients undergoing mechanical thrombectomy, as abrupt reperfusion induces secondary brain damages (De Meyer et al., 2016; Sutherland et al., 2016; Zhao et al., 2020). Therefore, alleviating ischemia-reperfusion injury after recanalization may further improve the functional outcomes of patients with ischemic stroke (Wills and Ding, 2020).

Ischemic post-conditioning is a promising therapeutic strategy in which several cycles of ischemia and reperfusion performed immediately after reflow confer protection against more severe injuries (Zhao et al., 2003). This strategy has been widely investigated in coronary heart disease. A randomized clinical trial indicated that ischemic post-conditioning reduced infarct size and edema caused by ischemia-reperfusion injury in patients with reperfused ST-segment elevation myocardial infarction (Thuny et al., 2012). A number of experimental studies using rodent animal models also demonstrated that ischemic post-conditioning reduced infarct volume and improved neurological outcomes, thereby inducing neuroprotection after stroke (Zhao et al., 2006; Esposito et al., 2015; Doeppner et al., 2017). However, whether ischemic post-conditioning has neuroprotective effects in patients with acute ischemic stroke undergoing mechanical thrombectomy remains unknown.

In this study, we plan to conduct a 3 + 3 dose-escalation trial to determine the safety and tolerability of ischemic post-conditioning incrementally for a longer duration of up to 5 min × 4 cycles in stroke patients undergoing mechanical thrombectomy. The present study, called the Ischemic Post- conditioning in Acute Ischemic Stroke Thrombectomy (PROTECT) study, will also provide the basis for a subsequent prospective study to explore the efficacy of ischemic post- conditioning.

## Methods

This is a single-center, phase-I, dose-escalation study to investigate the safety and tolerability of ischemic post-conditioning in stroke patients undergoing mechanical thrombectomy. This study was approved by the Local Ethics Committee of Tianjin Huanhu Hospital and registered at Clinicaltrials.gov (Identifier: NCT05153655; Registration date: 10 December 2021^1^). All patients will voluntarily sign an informed consent form before being enrolled in this study.

### Study design

The study protocol is designed with reference to the classical 3 + 3 drug trial (Hansen et al., 2014), which is generally used to determine the maximum tolerable dose of a drug in phase-I clinical study. The study design is illustrated in Figure 1. Specifically, the study starts with three patients in the 0 min group (sham operation). (a) If no major response (defined below) occurs in any of the three patients, 1 min × 4 cycles (1 min ischemia followed by 1 min reperfusion, and repeated for 4 cycles, total time 7 min) will be used. (b) If a major response occurs in one patient, then three more patients will be enrolled to further assess the safety and tolerability of the same duration (1 min × 4 cycles); if no additional major response occurs, the duration will be escalated to the next dose (2 min × 4 cycles; 2 min ischemia followed by 2 min reperfusion, and repeated for 4 cycles, total time 14 min); if an additional major response occurs, the study will be stopped, and the previous dose will be defined as the maximum tolerable duration of ischemic post-conditioning. (c) If a major response happens in 2–3 patients, the study will be stopped, and the previous dose will be defined as the maximum tolerable duration. The incremental schedule of the ischemia and reperfusion duration is 0, 1, 2, 3, 4, and 5 min × 4 cycles.

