**FIGURE 1 F1:**
[figure not shown]
The 3 + 3 dose-escalation trial design. The study starts with three patients. (a) If no major response occurs in any of the three patients, the next duration will be used. (b) If a major response occurs in one patient, then three more patients will be enrolled to further assess the safety and tolerability of the same duration; if no additional major response occurs, the duration will be escalated to the next dose; if an additional major response occurs, the study will be stopped, and the previous dose will be defined as the maximum tolerable duration of ischemic post-conditioning. (c) If a major response happens in 2–3 patients, the study will be stopped, and the previous dose will be defined as the maximum tolerable duration. The incremental schedule of the duration is 0, 1, 2, 3, 4, and 5 min × 4 cycles.

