### Major response

We pre-defined the major responses before the start of the study, which included any of the following adverse events during the procedure:

•Vessel perforation or rupture (angiography shows active contrast extravasation from the site of ischemic post-conditioning, and postprocedural head computerized tomography shows a high-density region in the corresponding area).•Reocclusion of the culprit vessel after ischemic post-conditioning.•Vessel dissection (angiography shows the typical appearance of dissection at the site of ischemic post-conditioning, such as intimal flap, double lumen, pseudoaneurysm, and long tapering stenosis).•Severe vasospasm requiring treatment.•Ischemic post-conditioning related thrombotic events (angiography shows *in situ* thrombosis or distal embolism after ischemia post-conditioning).•Rupture of the balloon used for ischemic post- conditioning.

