### Sample size

Since this is a 3 + 3 dose-escalation study with six doses (0, 1, 2, 3, 4, and 5 min), a minimum of 18 (6 groups × 3 patient/group) patients will be required, assuming no major response occurs at any dose level, and a maximum of 36 (6 groups × 6 patient/group) patients will be required, assuming one major response occurs at each dose level.

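### The dose labels in rule (b) do not fit the 0-min starting cohort: they name 1 min and 2 min where the Figure 1 legend and the 36-patient maximum require 0 min and 1 min

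*Protocol article*

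**What the plan says.** All references are to the protocol article.

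- **Study design, start:** "the study starts with three patients in the 0 min group (sham operation"). Rule (a) takes a cohort with no major response to 1 min × 4 cycles, so the cohort under judgement is the 0-min one.
- **Study design, rule (b), one response in three:** "three more patients will be enrolled to further assess the safety and tolerability of the same duration (1 min × 4 cycles"). If none of the added patients has a response, "the duration will be escalated to the next dose (2 min × 4 cycles; 2 min ischemia followed by 2 min reperfusion", and so on. If one does, the study stops.
- **Figure 1 legend, rule (b):** "three more patients will be enrolled to further assess the safety and tolerability of the same duration; if no additional major response occurs", the trial goes to the next duration. No dose is named.
- **Sample size:** "Since this is a 3 + 3 dose-escalation study with six doses (0, 1, 2, 3, 4, and 5 min"), with a minimum of 18 and a maximum of 36. The maximum is six groups of six; that many "patients will be required, assuming one major response occurs at each dose level".

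**The concern.** Rules (a), (b) and (c) are set out as the three possible outcomes of one cohort, and that cohort is at 0 min. Both labels in rule (b) are one level too high for it. The words of the rule (same duration, next dose) say one thing and the parentheses attached to them say another.

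This is the instruction that assigns occlusion times to patients, so the wording has consequences. Taken literally, one response in the sham cohort leads to three patients receiving four 1-min balloon occlusions, although the sham level has not been cleared. Those three patients then decide the 1-min level by themselves: no response among them sends the trial to 2 min, and a single response stops it. The 1-min level never gets the three-plus-three assessment that the Figure 1 legend gives to every level.

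**Working it through.** **1. The plan's own range.** There are six levels (0, 1, 2, 3, 4 and 5 min).
- Minimum: 6 × 3 = 18, as stated.
- Maximum: 6 × 6 = 36, as stated. This requires six patients at 0 min, so a response at 0 min must lead to expansion at 0 min.

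**2. The maximum under the printed labels**, with the Figure 1 rule at all later levels.
- Literal reading, one response at 0 min: 3 at 0 min, 3 at 1 min, then 6 at each of 2, 3, 4 and 5 min: 3 + 3 + 4 × 6 = 30.
- Rule (b) read as an example at 1 min, with 0 min never expanded: 3 + 5 × 6 = 33.

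Neither gives 36. Only the rule in the Figure 1 legend does.

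**3. How often the conflicting branch is reached.** The documents give no rate of major responses at 0 min. I assume a per-patient rate p of 1% or 5%, the same at 0 and 1 min, with independent patients and q = 1 − p. Low values are the more plausible, because five of the six events listed under Major response are tied to post-conditioning or its balloon (for example "Reocclusion of the culprit vessel after ischemic post-conditioning"); only severe vasospasm is not.

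| Quantity | Formula | p = 1% | p = 5% |
|---|---|---|---|
| Exactly one response in three at 0 min | 3pq² | 3 × 0.01 × 0.9801 = 2.9% | 3 × 0.05 × 0.9025 = 13.5% |
| Given that, a further response in a 0-min expansion | 1 − q³ | 1 − 0.9703 = 3.0% | 1 − 0.8574 = 14.3% |
| Both | 3pq²(1 − q³) | 0.1% | 1.9% |

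The last row is the chance that the Figure 1 rule would have stopped the study at 0 min while the literal text goes on to treat three patients at 1 min.

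**4. Does the literal text stop the study more often?** Take one response at 0 min as given, and look at the chance of stopping by the end of the 1-min level.
- Literal text: 1 − q³ = 3.0% and 14.3%.
- Figure 1 legend: 1 − q³(q³ + 3pq⁵) = 3.1% and 16.5%.

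At equal rates it does not; the literal text stops slightly less often.

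**The case against.** The strongest reply is that rule (b) is a running example: (a) takes the clean 0-min cohort to 1 min, and (b) then shows expansion at 1 min and escalation to 2 min. Both labels fit this reading, and so do the stated total times of 7 and 14 min. Study design also refers to Figure 1, whose legend gives the general rule, and Sample size counts 0 min as a level that can hold six. An investigator who saw the conflict would probably follow the figure.

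Much of this stands. There is one recoverable intent, and the design itself is not in question. But the text does not mark a shift from 0 to 1 min, and if the shift is granted, Study design alone has no rule for one response at 0 min. On either reading the section does not agree with the count of 36.

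A reader might infer more than the documents support:
- **That the trial could outgrow its planned size.** It could not. The alternative counts, 30 and 33, lie below 36, and 33 is also what the Figure 1 rule gives when no response occurs at 0 min. They show an inconsistency, not an overrun.
- **That the problem is frequent.** At assumed sham rates of 10% or 20% the branch would be reached in 24.3% or 38.4% of trials, but nothing in the documents points to rates that high at 0 min.
- **That the design lacks a result for a stop at 0 min.** The text resolves a stop to the level below, and none exists below 0 min. This is a detail that a condensed article may leave out, and its answer is obvious: no tolerable duration is established. It is not part of this point.

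**Conclusion.** The point holds as an inconsistency in an operative rule. The labels in rule (b) of Study design are wrong for the cohort with which the study starts, and they disagree with the Figure 1 legend and with the basis of the 36-patient maximum.

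The practical risk is small. At assumed sham rates of 1% and 5%, the branch arises in about 3% and 13.5% of trials, and harm would also require staff to follow the parenthesis over the figure. These percentages rest on assumed rates and on independence between patients. The inconsistency itself rests only on the text. The Figure 1 image was not available, so the comparison is with its legend.

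Correction is still warranted: the Discussion in the abstract presents this as the first clinical study of the procedure in this setting, and those applying a dose-assignment rule should not have to reconstruct it from the sample-size count.

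**What to change.** In rule (b) of Study design, delete the parenthesis naming 1 min × 4 cycles and the one naming 2 min × 4 cycles. The rule then reads as in the Figure 1 legend: expand at the level where the response occurred, 0 min included, and then go to the next level. The timing detail lost with the second parenthesis (14 min in total) can move to the sentence that lists the schedule. Alternatively, relabel the two parentheses 0 min and 1 min; deletion is cleaner, because the rule then serves every level.

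The cost is an edit to one paragraph. No patients or data are added, the Figure 1 legend stays as it is, and the range of 18 to 36 is unchanged.

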**FIGURE 1 F1:**
[figure not shown]
The 3 + 3 dose-escalation trial design. The study starts with three patients. (a) If no major response occurs in any of the three patients, the next duration will be used. (b) If a major response occurs in one patient, then three more patients will be enrolled to further assess the safety and tolerability of the same duration; if no additional major response occurs, the duration will be escalated to the next dose; if an additional major response occurs, the study will be stopped, and the previous dose will be defined as the maximum tolerable duration of ischemic post-conditioning. (c) If a major response happens in 2–3 patients, the study will be stopped, and the previous dose will be defined as the maximum tolerable duration. The incremental schedule of the duration is 0, 1, 2, 3, 4, and 5 min × 4 cycles.

### Major response

We pre-defined the major responses before the start of the study, which included any of the following adverse events during the procedure:

•Vessel perforation or rupture (angiography shows active contrast extravasation from the site of ischemic post-conditioning, and postprocedural head computerized tomography shows a high-density region in the corresponding area).•Reocclusion of the culprit vessel after ischemic post-conditioning.•Vessel dissection (angiography shows the typical appearance of dissection at the site of ischemic post-conditioning, such as intimal flap, double lumen, pseudoaneurysm, and long tapering stenosis).•Severe vasospasm requiring treatment.•Ischemic post-conditioning related thrombotic events (angiography shows *in situ* thrombosis or distal embolism after ischemia post-conditioning).•Rupture of the balloon used for ischemic post- conditioning.

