### Data Safety Monitoring Board

The PROTECT study will establish an independent Data Safety Monitoring Board to evaluate all the safety profiles. In addition to the above-mentioned major responses, any serious adverse events occurring during hospitalization, whether or not related to ischemic post-conditioning, must be reported to the Institutional Review Board within 24 h of their occurrence, pending review by the Data Safety Monitoring Board after investigators provide relevant data.

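### The maximum tolerable duration is set only by vascular and device events seen during the procedure, so it does not reflect delayed or purely clinical harm

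*Protocol article*

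**What the plan says.** The Abstract (Background) gives the aim: "This study aims to determine the safety, tolerability, and maximum tolerable duration of ischemic post-conditioning". Under Study design, every decision depends on the number of major responses. Escalation follows "If no major response (defined below) occurs in any of the three patients". One response in three leads to expansion: "then three more patients will be enrolled to further assess the safety and tolerability of the same duration". A further response in the added three, or two or three responses in the first three, stops the study and makes the previous duration the maximum tolerable one.

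The Major response section restricts the count to events "which included any of the following adverse events during the procedure". It lists six:
- vessel perforation or rupture
- reocclusion of the culprit vessel
- dissection
- severe vasospasm needing treatment
- thrombotic events related to post-conditioning
- balloon rupture

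The Abstract (Methods) gives the same six, ending "rupture of the balloon used for ischemic post-conditioning) as the stopping rules". One item mentions later imaging, "and postprocedural head computerized tomography shows a high-density region in the corresponding area", but only together with contrast extravasation on angiography.

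The Data Safety Monitoring Board section sets up an "independent Data Safety Monitoring Board to evaluate all the safety profiles". Separately from the major responses, it requires any in-hospital serious adverse event to be reported within 24 h, pending the board's review. It does not say that such an event can delay escalation, count as a major response or change the declared duration.

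**The concern.** The quantity being escalated is occlusion time: 4 × 1 to 4 × 5 min, so 4 to 20 min of total re-occlusion across the active levels. Harm from longer re-occlusion could plausibly appear after the patient leaves the angiography suite, as hemorrhage, neurological worsening or death. The decision count closes before then. Procedures also permits general anesthesia, under which a clinical change may not be visible during the counted period.

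The Discussion raises the worry about transient ischemia and answers it by argument: a single occlusion stays below the time to neuronal death, collaterals supply blood, and hours of ischemia came before. The declared duration cannot test that argument. Study design nevertheless presents the count as an assessment of safety and tolerability, and the Conclusion carries the duration forward as the starting point for efficacy studies. What is at stake is the meaning of the number handed to the next trial.

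**Working it through.** **The plan's own figure.** Sample size gives 18 to 36 patients. Six levels × 3 = 18 and six levels × 6 = 36, so it reproduces. Counting more kinds of event leaves this range unchanged.

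**Inputs.** The escalation rule comes from Study design. The article gives no event rates, so all rates here are assumptions: procedural major responses p (mainly 2% per patient) and related post-procedural events q (5% to 30%). The two are taken as independent and constant across levels.

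**Formula.** With per-patient probability r of a counted event, a level clears if 0 of 3 respond, or if 1 of 3 responds and then 0 of 3 more:

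f(r) = (1−r)³ + 3r(1−r)² × (1−r)³ = (1−r)³ + 3r(1−r)⁵

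Under the written rule r = p. If related events count, r = 1 − (1−p)(1−q). The chance of a stop over the five active levels is 1 − f(r)⁵.

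**If related events counted, p = 2%.**

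| q | r | Level clears | Stop within five levels |
|---|---|---|---|
| any q, written rule | 0.020 | 0.995 | 0.023 |
| 5% | 0.069 | 0.952 | 0.219 |
| 10% | 0.118 | 0.875 | 0.487 |
| 20% | 0.216 | 0.674 | 0.861 |
| 30% | 0.314 | 0.466 | 0.978 |

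Under the written rule, q has no effect. Per level, the difference is small at 5% (0.995 − 0.952 ≈ 0.04) and large at 30% (0.995 − 0.466 ≈ 0.53). With p = 5%, the written rule clears a level with probability 0.973; counting gives 0.910, 0.824, 0.622 and 0.425 at the same four values of q.

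**Cost for a harmless intervention.** Suppose 3–5% of patients have an event wrongly attributed to post-conditioning. At p = 2% and 3% wrongly attributed, r = 1 − 0.98 × 0.97 = 0.0494, f = 0.974 and 1 − f⁵ = 0.123. The chance of a stop over five active levels is then:

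| p | Written rule | 3% wrongly attributed | 5% wrongly attributed |
|---|---|---|---|
| 0% | 0 | 0.049 | 0.126 |
| 1% | 0.006 | 0.083 | 0.171 |
| 2% | 0.023 | 0.123 | 0.219 |
| 5% | 0.126 | 0.270 | 0.375 |

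**Same scale.** At p = 2%, a true related rate of 5% and a wrongly attributed rate of 5% both stop the study with probability 0.219. The counting rule cannot tell them apart; all of the discrimination comes from the board's judgment of relatedness.

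**All-cause counting.** At an illustrative 15% all-cause rate, a harmless intervention would be stopped with probability 0.64 (p = 0) or 0.71 (p = 2%). The Introduction cites mortality above 15% after thrombectomy but gives no early-window rate, so the 15% is only an order of magnitude. It is enough to rule out all-cause counting.

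**The case against.** The strongest defense is that this is a coherent, pre-specified choice. The six events are direct harms of inflating a balloon in a freshly reperfused artery, repeat angiography is required, and attribution is comparatively clear. Symptomatic hemorrhage, deterioration and death can also follow the stroke or the thrombectomy. With three to six patients per level, a board has little basis for attributing a single event. Safety and tolerability are stated beside the maximum tolerable duration, so the duration need not carry all the safety evidence, and the Conclusion calls it only a starting point. Much of this stands. It is why all-cause counting is wrong and why keeping the procedural definition under a narrower label is acceptable.

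Three stronger readings are tempting, and the documents do not support them:

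- **None of the six events registers neurological harm.** Reocclusion, thrombosis, distal embolism and perforation are direct causes of recurrent ischemia or hemorrhage, and they are counted. The gap is delayed or purely clinical harm.
- **The trial would carry on through a run of ward hemorrhages.** Read literally, three related ward hemorrhages in three patients still satisfy the escalation condition. But the board evaluates all safety data, and its power to hold the trial may lie in a charter that an article would not reproduce. Its absence here is not a fault in safety monitoring.
- **Counting related events would bring a large, known gain.** The gain is large only at assumed rates of 20–30%, and nothing in the article points to such rates.

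The condensed format of an article does not remove the remaining point: the article states the counted events, their time window and the declaration rule.

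**Conclusion.** The point holds as a modest, inexpensive improvement. As written, the maximum tolerable duration measures procedural tolerability. Delayed or purely clinical harm is collected but has no stated bearing on escalation or on the declared result, while the stated aim is broader. This is a weakness in what the declared duration means; the sample size is unaffected.

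The benefit of counting related events cannot be sized from the documents. The illustrative figures rest on assumed rates, independence and a constant risk across levels, and they show a real cost in false stops that depends on how well relatedness is judged. Board review before each escalation and a label that matches the rule do not depend on those figures.

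**What to change.** In Study design and the Data Safety Monitoring Board section, require the board to review each cohort's in-hospital serious adverse events over a fixed early window (for example 72 h) before the next duration opens. State in Major response that such an event counts only if the board judges it related to post-conditioning, never on an all-cause basis. Set the window before the first patient.

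If the sponsor prefers to keep the procedural definition, report the result as the maximum procedurally tolerated duration, tabulate in-hospital serious adverse events by duration beside it, and do not present it as overall safety and tolerability.

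**Cost.** The reports are already required within 24 h, so the first option adds board review, a short pause between cohorts and the false stops estimated above. The relabeling costs only wording and one descriptive table, with no added risk of a false stop.
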